# Effectiveness of the KC@H programme compared with clinic-based rehabilitation in patients recovering from ACL reconstruction: a study protocol for a single-centre, two-arm, single-blinded, randomised controlled superiority trial

**DOI:** 10.1136/bmjsem-2023-001868

**Published:** 2024-02-21

**Keywords:** Anterior cruciate ligament, Exercise rehabilitation, Knee ACL, Sports rehabilitation programs, Sports & exercise medicine

## Abstract

Patients who cannot fully comply with conventional clinic-based rehabilitation (CR) sessions after ACL reconstruction (ACLR) may find additional internet-based sessions beneficial. These remote sessions include therapeutic exercises that can be done at home, potentially extending the reach of rehabilitation services to underserved areas, prolonging the duration of care and providing improved supervision. The study’s main purpose is to determine if the Knee Care at Home (KC@H) programme is more effective than conventional CR alone in improving patient-reported, clinician-reported and physical functional performance outcome measures after ACLR. Additionally, the trial assesses the significance of changes in outcome measures for clinical practice.

This protocol outlines a randomised controlled trial for postoperative recovery following ACLR. Adult participants of both sexes who meet specific criteria will be randomly assigned to either the CR group or the KC@H group. Only the latter group will receive internet-based sessions of therapeutic exercises at home and CR sessions. A follow-up evaluation will be conducted for both groups 12 weeks after the intervention ends.

The trial protocol was approved by the Ethics Committee of the Universidade de Évora and complies with the Code of Ethics of the World Medical Association. All recordings will be stored on a secure server with limited access and deleted as soon as they are no longer needed.

The KC@H programme is expected to be superior to conventional CR for patients recovering from ACLR across multiple outcome measures. Also, the programme has the potential to promote superior recovery and extend the reach and duration of care.

Trial registration number: NCT05828355.

WHAT IS ALREADY KNOWN ON THIS TOPICCommunication technologies are being used for home-based rehabilitation after ACL reconstruction (ACLR). More data are needed to confirm their effectiveness compared with face-to-face rehabilitation.WHAT THIS STUDY ADDSBy demonstrating the effectiveness of the Knee Care at Home (KC@H) programme in maximising the recovery of patients after ACLR, we can offer healthcare professionals an innovative and complemental approach.HOW THIS STUDY MIGHT AFFECT RESEARCH, PRACTICE OR POLICYThe KC@H programme has the potential to expand the reach of rehabilitation services to underserved areas, prolong the duration of care and improve supervision using existing communication technologies.

## Background

Injuries to ACL can result in significant functional limitations.^1^ Thus, many physically active individuals often undergo ACL reconstruction (ACLR).^1^ Following surgery, individuals typically adhere to extensive and time-consuming clinic-based rehabilitation (CR) protocols essential for a complete recovery.^2 3^ These protocols involve executing therapeutic exercises guided by physiotherapists in CR sessions to alleviate knee pain, improve knee function and reduce the risk of further ACL injury.^3^

Postoperative progression in conventional CR stages requires support from standardised and evidence-based clinical guidelines. Currently, these guidelines are still being debated in the scientific literature.^3 4^ Progression is usually built on time-based principles, but experts have introduced criteria-based standards to improve the decision-making framework.^5^ As a result, conventional CR lacks consistency in its content and individual patient exposure.^4^ Each stage of recovery is distinct and relies on the patient’s expectations and progression over time.^4^

Due to each patient’s varying guidelines and progression criteria, physiotherapists face challenges in providing consistent care.^4^ This may contribute to some patients being unable to fully regain their pre-injury level of function and participate in strenuous activities.^3^

The ongoing debate surrounding evidence-based clinical guidelines is not the only concern regarding conventional CR protocols. There are also worries about the effectiveness of these protocols due to planning issues.^2^ Additionally, there is a significant gap between the completion of CR protocols and the return to normal activity levels, with some patients only attending a limited number of treatments and follow-up visits.^6^ When inadequate planning is combined with limited patient involvement, crucial clinical and functional outcomes can be disrupted.^7^

To address challenges in obtaining CR and enhance patient engagement, healthcare professionals recommend extended periods of personalised supervision tailored to patients’ specific needs and daily schedules.^4 7^ This increased supervision can potentially improve communication among healthcare professionals.^8^

Healthcare professionals can enhance patient involvement and engagement and reduce the previously described gap by incorporating internet-based interventions alongside CR.^8 9^ However, ensuring easy access to these interventions and integrating them with CR are crucial rather than using them in isolation.^9^

In recent years, several approaches have been using communication technologies to deliver rehabilitation services to individuals at their homes following ACLR.^10^ While some evidence suggests that these approaches may be equally beneficial as conventional CR, the available data are insufficient to support their effectiveness in patient- and clinician-reported outcomes fully.^11^

Internet-based interventions can potentially improve postoperative recovery by ensuring treatment continuity and providing patients with real-time feedback.^8 9^ This can be especially beneficial for those with difficulty accessing a rehabilitation clinic, as they can perform exercises at home.^12^

Additionally, it can reduce the need for travel and the cost of consultations.^8^ However, access to innovative approaches for ACLR recovery may be limited due to government organisations’ lack of prioritisation of orthopaedic services.^12^

The Knee Care at Home (KC@H) programme incorporated a new supplemental method to enhance conventional rehabilitation practises following ACLR. It includes an internet-based intervention with synchronous supervision of therapeutic exercises at home through videoconferencing software (remote sessions) and conventional CR (face-to-face sessions).

As such, this trial aims to determine whether the KC@H programme is more effective than conventional CR alone in improving patient-reported, clinician-reported and physical functional performance outcome measures after ACLR. Additionally, the trial assesses the significance of clinical changes in outcome measures for clinical practice.

## Methods

### Trial design

This protocol details the implementation of a randomised, controlled, parallel-group, two-arm, single-centre superiority trial. The allocation ratio is 1:1, and the protocol follows the Standard Protocol Items Recommendations for Interventional Trials Statement.^13^

A flow chart illustrates the trial procedures (figure 1). The study begins 2 weeks after hospital discharge and consists of a 22-week intervention period, followed by a 36-week follow-up. This protocol is being conducted simultaneously with a feasibility study.

**Figure 1 F1a:**
[figure not shown]
Flow chart of trial procedures.

#### Availability of data and materials

All records are kept on a secure server, and only the orthopaedic surgeon and the team’s principal investigator can access them. If any medical or research records need to be copied, the participant’s name and any other information will be removed. No personal information, such as name, address or telephone number, will leave the Hospital da Misericórdia de Évora (HME) database. All the information gathered for this investigation will be deleted or destroyed as soon as it is no longer needed.

### Sample selection and recruitment

Participants will be recruited at HME in Portugal. During their preoperative consultation with the orthopaedist, all patients with ACL rupture who are scheduled for ACLR at HME will be identified for recruitment. They will be given an informed consent form containing information on the trial protocol. Patients who agree to participate will receive a KC@H programme manual structured based on the Consensus on Exercise Reporting Template recommendations.^14^

### Study setting

Under the KC@H programme, a certified exercise and health coach will supervise synchronous remote sessions of therapeutic exercises at home, using internet-based videoconferencing software. Individualised face-to-face sessions with a physiotherapist will also be available for conventional CR participants at public or private rehabilitation clinics, depending on participant preference and availability. Outcome measures will be evaluated during scheduled consultations at the HME, except for pain intensity and physical exertion, which will be assessed during each remote session.

### Patient and public involvement statement

Patients and/or the public were not involved in the design, conduct, reporting, or dissemination plans of this research.

### Eligibility criteria

Adults of any sex who meet all eligibility criteria and provide written informed consent will be recruited for participation during the first postoperative consultation, which takes place 2 weeks after hospital discharge.

#### Inclusion criteria

Undergone primary ACLR regardless of surgical method and choice of autograft.Aged between 18 and 55 years at the time of ACLR.Have a healthy contralateral (opposite) knee.The time between ACL injury and ACLR should not exceed 12 months.

#### Exclusion criteria

Declined to participate.Concomitant osteochondral injuries.Undergone multiple reconstructions of the lateral collateral ligament or posterior cruciate ligament.Significant lower limb injuries within the 12 months before the ACL injury.Medical conditions that may affect recovery.Using medication for mental health disorders.Severe impairments in communication or balance.

### Group allocation

After confirming eligibility, participants will be randomly assigned (in a 1:1 ratio) to either the CR or KC@H group during the first postoperative consultation. Covariate adjustment will be conducted to ensure homogeneity in age and sex. Considering the covariates, the randomisation sequence will be tested using the ‘ralloc’ STATA module. The participants and the outcome assessor will be blinded to the allocation procedures.

A computer or tablet with an internet connection is required for those assigned to the KC@H group. Additional training will be provided for using the internet-based videoconferencing software, the Visual Analogue Scale (VAS) for pain^16^ and the Borg Category Ratio Scale (CR10) for physical exertion.^17^

### Blinding

Participants, orthopaedists and coaches will be informed about the group allocation during the trial, while the outcome assessor will remain blinded. The assessor will not be involved in any other aspects of the trial and will be explicitly instructed not to discuss group allocation with participants. Participants and orthopaedists will be instructed to refrain from discussing group allocation with the assessor.

### Trial retention

Retention strategies include participant trial identity cards (patient number only). Other strategies include emails or short messages sent by orthopaedists, exercise and health coaches during participant follow-up.

### Preoperative consultation

During the preoperative consultation, several activities are carried out. These include identifying potential participants for recruitment, obtaining informed consent, collecting sociodemographic data (such as age, sex assigned at birth, lower limb dominance, injury characteristics, mechanism of injury, time from injury to ACLR, smoking habits, education level and occupational status), assessing patient-reported outcomes (such as pain, symptoms, quality of life, swelling, catastrophising, anxiety, depression and stress), evaluating clinician-reported outcomes (such as height, weight, knee range of motion, thigh muscle length and thigh muscle strength) and providing training on videoconferencing software, pain scale and physical exertion scale.

### After surgery

Following ACLR, the surgical procedure details will be promptly documented in the participant’s medical record. Additionally, for the first 2 weeks after ACLR, participants will be sent a daily text message containing a link to an online questionnaire. This questionnaire is designed to assess pain intensity and pain management strategies.

### First postoperative consultation

Participants will have their first postoperative consultation 2 weeks after being discharged from the hospital. During this consultation, they will be assessed for eligibility and randomly assigned to either the CR or KC@H groups. An orthopaedist and a physiotherapist (assessor) will evaluate outcome measures at baseline.

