#### KC@H programme manual

The KC@H manual describes all therapeutic exercises included in the programme, with patient progression determined based on objective criteria rather than a predetermined recovery timeline after ACLR.^19^ This approach, which combines time- and criterion-based standards, helps prevent adverse events during remote sessions and allows the intervention to be applied in various clinical scenarios.^19^

Due to the unavailability of specialised strength equipment for our remote sessions, we have used the CR10 scale to monitor training load and progress. For every exercise, we will record the duration (in minutes), number of sets and repetitions and the level of completion (complete, incomplete, unable to perform). Additionally, we will document the pain intensity at the start and end of each remote session. The orthopaedist will receive a detailed progress report containing all the information gathered during the remote sessions.

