#### Outcomes measures and assessments

Outcome measures will be assessed during scheduled consultations with the orthopaedist. The exercise and health coach will record pain intensity and physical exertion during each remote session. A physiotherapist (assessor) will remain consistent for every evaluation and conduct assessments during consultations with the orthopaedist.

The outcome measures and assessment tools for both groups are categorised into patient-reported (table 2), clinician-reported (table 3), physical functional performance and clinical relevance (table 4). These tables outline the procedures for each outcome measure and the tools used in the evaluations.

**Table 2 T2:** Patient-reported outcome measures

Outcome	Assessment tool	Procedures
Knee pain during the last 24 hours	Visual Analogue Scale^16^	Patients provide feedback on knee pain intensity by marking a point on a 100 mm straight horizontal line. The beginning of the line represents ‘no pain’, while the end represents the ‘worst possible pain’. A ruler measures the distance (millimetres) from 0 to the patient’s marking. A numerical value and Wong-Baker faces scale will also be presented to the patient for reference.
Knee pain during the last week	Knee Injury and Osteoarthritis Outcome Score (KOOS)^22^	Patients provide feedback on the severity of their knee pain using a standard 5-point Likert scale. Each response option is assigned a numerical value (0 for none, 1 for mild, 2 for moderate, 3 for severe and 4 for extreme). A score of 0 indicates no pain, while a score of 32 (based on 8 questions) indicates extreme pain.
Knee symptoms and stiffness during the last week	KOOS^22^	Patients are asked to rate their knee symptoms and stiffness using a standard 5-point Likert scale, with each response option assigned a numerical value (0, 1, 2, 3, 4). A score of 0 indicates total absence of symptoms, while a score of 20 (based on 5 questions) indicates constant symptoms. For knee stiffness, a score of 0 indicates total absence, while a score of 8 (based on 2 questions) indicates extreme stiffness.

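### Assessor blinding rests on instructions and role separation alone: a role left unblinded co-evaluates baseline outcomes, and no stated order puts blinded measurement before allocation or before the consultation

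*Protocol article*

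**What the plan says.** The Blinding section of the protocol article sets out who knows the allocation: "Participants, orthopaedists and coaches will be informed about the group allocation during the trial, while the outcome assessor will remain blinded". It gives three safeguards. The assessor has no other part in the trial. The assessor "will be explicitly instructed not to discuss group allocation with participants". And "Participants and orthopaedists will be instructed to refrain from discussing group allocation with the assessor".

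The section on the first postoperative consultation, which is the baseline visit t0, says of the patients that "they will be assessed for eligibility and randomly assigned to either the CR or KC@H groups". It goes on: "An orthopaedist and a physiotherapist (assessor) will evaluate outcome measures at baseline".

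For the evaluations in general, the section on outcome measures and assessments says: "A physiotherapist (assessor) will remain consistent for every evaluation and conduct assessments during consultations with the orthopaedist". The section on postoperative phases orders things differently: at weeks 8, 12, 20 and 24 (t2, t3, t5, t6) it has an evaluation that comes after the consultation.

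The KC@H programme manual section adds: "The orthopaedist will receive a detailed progress report containing all the information gathered during the remote sessions". Table 1 gives remote sessions to the intervention arm only. The Statistical analysis section adjusts all models for baseline.

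**The concern.** The trial is titled single-blinded, and the blinded party is the outcome assessor. Two features of the stated procedures put strain on that.

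First, a role that the Blinding section leaves unblinded is named as an evaluator of outcomes, at the same visit at which allocation takes place. If any t0 measurement is made after allocation is known, the baseline is no longer a clean pre-randomisation covariate.

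Second, the assessor works in, or straight after, a consultation between two people who both know the arm, one of whom holds information that only KC@H patients generate. An instruction not to discuss allocation with the assessor does not cover what the assessor may overhear or see.

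At stake are two of the three outcome families in the trial aim, the clinician-reported and the physical performance measures. Effusion by palpation, passive extension with pressure applied by the assessor, and hand-held dynamometry depend on the assessor's handling. Assessor blinding is the only blinding that these outcomes have.

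**Working it through.** The plan states no figure on this point, so the check sets the sections side by side.

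**1. Who is unblinded.** Blinding: participants, orthopaedists and coaches. The Group allocation section says that participants and the assessor are blinded to the allocation procedures. That can be read as concealment of the sequence, and it does not make the orthopaedist blinded.

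**2. Who evaluates outcomes.** At t0: an orthopaedist and the physiotherapist assessor (First postoperative consultation). At later visits only the physiotherapist is named (Outcomes measures and assessments). The overlap between an unblinded role and outcome evaluation is therefore documented at t0 only, and the protocol does not say which t0 measures the orthopaedist takes.

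**3. Order at t0.** Eligibility, allocation and the t0 outcomes fall in one visit (Group allocation, First postoperative consultation, Table 5). The text mentions allocation first but fixes no sequence. Postoperative phases says that the intervention stage starts after the baseline evaluation. This places measurement before treatment, not before allocation.

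**4. Order at later visits.** One section has the assessments during the consultation; another has the evaluation after it at t2, t3, t5 and t6. Neither puts the blinded measurement first.

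**5. What carries arm information.** The remote-session report goes to the orthopaedist and can exist only for a KC@H patient. No section says that it is opened or discussed in the assessor's presence.

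**6. Which outcomes are exposed.**

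| Outcome type | At t0 | After t0 |
|---|---|---|
| Assessor-measured: effusion, range of motion, muscle length, strength, stair test; hop test from week 16 | Exposed if measured after allocation, or by an unblinded evaluator (hop test not done at t0) | Exposed if the assessor learns the arm |
| Self-reported: KOOS pain and the rest of Table 2 | Exposed if completed after the patient learns the arm | Participants know their arm; assessor blinding gives no protection either way |

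**7. Direction of a t0 error.** In a baseline-adjusted comparison, the adjusted effect is the follow-up difference minus β times the t0 difference, where β is the slope on baseline. If knowledge of the arm shifts t0 in KC@H by d, the error is −β·d. With β positive and higher scores better, an upward shift lowers the estimated KC@H effect and a downward shift raises it. The net direction cannot be predicted.

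**8. Purely illustrative sensitivity.** Suppose, as an assumption with no source in the documents, that unblinding moves an assessor-rated outcome by b SD in favour of KC@H. With 28 per arm and a two-sided 5% z-test, the shift in the test statistic is b·√(28/2) = b·√14. For b = 0.1, 0.2 and 0.3 the shift is 0.37, 0.75 and 1.12, and the rejection rate under no true effect is 6.6%, 11.6% and 20.2%. This is a simple two-sample test at one time point, with the number per arm before any dropout and no t0 error. It is not the planned mixed model and does not estimate the bias in this trial.

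**The case against.** The case for leaving the text alone has real substance.

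- The safeguards are more than a token. The assessor has no other trial role, and assessor, orthopaedists and participants are all bound not to discuss allocation. The section on availability of data and materials restricts records to the orthopaedic surgeon and the principal investigator, which would seem to keep the assessor away from stored session reports. A reader might infer that blinding is unprotected; the text does not support that.
- Consultation also serves as the name of the visit: every column of Table 5 carries it. Assessment during a consultation may mean no more than on the same day.
- A reader might infer that KC@H progress is reviewed in front of the assessor. The protocol says only that the orthopaedist receives a report.
- A reader might infer that the orthopaedist evaluates outcomes throughout. That is stated for t0 only.
- A reader might infer that t0 is measured after allocation. That rests on sentence order within a description of one visit.
- A minute-by-minute running order is detail that a condensed article may leave to the full protocol.

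Most of this stands, and it limits the point. It does not remove three things that are stated and not merely omitted: an unblinded role is named as outcome evaluator at the randomisation visit; two sections give different orders for consultation and evaluation; and neither order puts the blinded measurement first. Restricted access to records also does not govern what is said in the room.

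**Conclusion.** The point holds in a limited form. Assessor blinding is stated and has some protection, but that protection consists of non-disclosure instructions, the assessor's lack of another trial role, and a general rule on access to records. No section separates the assessor from the consultation or places t0 measurement before allocation. The sections on blinding, the first postoperative consultation, postoperative phases and outcome assessment need to be reconciled.

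After t0 the risk is confined to assessor-measured outcomes. KOOS pain, on which the sample size rests, and the other self-reports are affected only through the order at t0.

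No size can be derived from the documents. The illustrative rejection rates rest on assumed biases and should not be quoted as expected error rates. Nor do the documents show that unblinding will occur. The conclusion assumes that the article's wording reflects the procedures in use; if the full protocol already fixes the order as proposed below, only the article's wording needs correcting. The change is worth making because it is cheap and protects both the baseline covariate and the outcomes that depend on the assessor's handling.

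**What to change.** Reconcile the four sections by stating the following.

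1. **At t0:** all outcomes, self-reported and measured, are completed after eligibility is confirmed and before allocation is drawn or disclosed to anyone at the visit. The orthopaedist may still see the patient first to confirm eligibility, since no allocation exists at that stage.
2. **Evaluator:** only the blinded physiotherapist evaluates outcomes. If the orthopaedist must take a measure, name it and report it as unblinded.
3. **After t0:** the assessor works apart from the orthopaedist's consultation, preferably before it, and has no access to remote-session reports. State this in place of the two differing orders.

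The cost is a rewording and a small change to visit flow, with the orthopaedist at times waiting for the assessor to finish. The Trial status section says that the protocol was submitted before recruitment began. If visits have since taken place, record the order actually followed, apply the new order to the remaining visits, and describe both in the trial report.
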